### **Inclusion criteria**

1. ME/CFS according to Canadian consensus criteria (2003) (1); moderate (mainly housebound) to severe (mainly bedridden) disease.
2. Age 18 to 65 years.
3. Signed informed consent.
4. Duration of ME/CFS disease at least two years.
5. The ME/CFS disease should have a defined onset, e.g. after an initial infection or other immunological trigger.

6. For females of childbearing potential: Negative serum pregnancy test.

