#### **Daratumumab dosing, injection, and injection-related reactions (IRR)**

Daratumumab subcutaneous injections will be given at a fixed dose of 1800 mg. A 15 ml syringe, which also contains recombinant hyaluronidase, is injected over 3-5 minutes into the abdomen approximately 7-8 cm to the right or left of the umbilicus (rotating injection sites for successive injections), on intact, healthy skin.

The patient will stay in the outpatient ward for at least 6 hours after the first Daratumumab injection, for observation of any injection-related reactions (IRR). Intravenous access will be established before the injection for administration of premedication and will be maintained throughout the observation period. Any allergic reactions or IRR will be treated according to standard hospital procedure.

If no IRR after the first injection, the observation period following the subsequent three injections will be 2 hours.

IRR after subcutaneous injections occurred in 9% of patients with multiple myeloma after the first injection, usually of grade 1-2. The risk of IRR will probably be lower in these patients without malignant plasma cells due to the low number of CD38 positive plasma cells. In the small patient series using daratumumab in autoimmune diseases, IRR was not reported to be a clinical problem.

If a patient suffers a severe allergic reaction or injection-related reaction (grade 4), the patient will not receive further daratumumab intervention.

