#### Discontinuation of study intervention

In rare instances, it may be necessary for a participant to permanently discontinue study intervention. If study intervention is permanently discontinued, the participant should, if at all

possible, remain in the study to be evaluated for safety and efficacy as described under “Assessment during follow-up”.

A participant may be withdrawn at any time at the discretion of the investigator for safety reasons, if the investigator considers that further intervention may present a danger to the patient’s health. If a patient suffers a severe allergic reaction or injection-related reaction (grade 4), the patient will not receive further daratumumab intervention.

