## Adverse events and Safety board

### Adverse events

Investigators will assess and classify adverse events (AE), serious adverse events (SAE), and SUSAR (suspected unexpected serious adverse reactions) according to the Common terminology criteria for adverse events (CTCAE), version 5.0 and the study drug SmPC.

For the purpose of safety and toxicity assessment, adverse events from grade 2 (moderate) and upwards, with possible, probable or certain causal relationship with the study drug will be reported. All SAE will be reported, regardless of causality.

Elective or pre-planned hospital admissions arranged prior to the start of study, or planned hospital admissions for trial specific procedures or treatment are not considered SAE.

Definitions and procedures for assessments and reporting of adverse events are described in appendix 1.

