### Adverse event/ serious adverse event

#### Definition of adverse events (AE)

An Adverse Event (AE) is any untoward medical occurrence in a patient administered a pharmaceutical product and which does not necessarily have to have a causal relationship with this treatment. It can therefore be any unfavorable and unintended sign, symptom, or disease temporally associated with the use of a medicinal product, whether or not considered related to the medicinal product. This includes any occurrence that is new in onset or aggravated in severity from the baseline condition, or abnormal results of any diagnostic procedures, including laboratory testing abnormalities.

All toxicity will be graded according to Common Terminology Criteria for Adverse Events (CTCAE) guidelines (version 5.0).

Adverse events will be graded using the following criteria:

- Grade 1 (Mild): discomfort noticed but no disruption of normal daily activity.
- Grade 2 (Moderate): discomfort sufficient to reduce or affect normal daily activity.
- Grade 3 (Severe): inability to work or perform normal daily activity.
- Grade 4 (Life-threatening or disabling): represents an immediate threat to life.

Furthermore, adverse events will be classified into serious adverse event (SAE) yes/no.

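### The mandatory stopping rule pairs the word severe with grade 4, but Appendix 1 gives that word to grade 3, so the rule is unclear for a grade 3 reaction

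*Protocol*

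**What the plan says.** The stopping rule appears twice in the Protocol. Under Daratumumab dosing, injection, and injection-related reactions (IRR) it reads: "If a patient suffers a severe allergic reaction or injection-related reaction (grade 4), the patient will not receive further daratumumab intervention". Under Discontinuation of study intervention it returns in the same words: "severe allergic reaction or injection-related reaction (grade 4), the patient will not receive further daratumumab intervention". Just before that second statement, the investigator is allowed to withdraw a participant whenever safety calls for it.

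Appendix 1, Definition of adverse events (AE), defines the grades. The second of its four steps is worded by activity: "Grade 2 (Moderate): discomfort sufficient to reduce or affect normal daily activity". The third step carries the label that the stopping rule uses, and it too is worded by activity: "Grade 3 (Severe): inability to work or perform normal daily activity". The fourth has a different label and is described by danger to life instead: "Grade 4 (Life-threatening or disabling): represents an immediate threat to life".

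The same section first states that all toxicity is graded by CTCAE version 5.0. It then introduces this list as the criteria by which adverse events will be graded.

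The main text, under Adverse events, uses the appendix's labels when it sets the reporting threshold: "adverse events from grade 2 (moderate) and upwards, with possible, probable or certain causal relationship with the study drug will be reported". Inclusion criterion 1 requires "moderate (mainly housebound) to severe (mainly bedridden) disease".

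**The concern.** A rule that ends treatment should give the same answer to everyone who applies it. Here the adjective points to grade 3 and the number to grade 4, and nothing says which prevails. Two investigators acting in good faith could treat the same grade 3 reaction differently: one as a required stop, the other as a matter for judgement. The discrepancy concerns whether a patient is re-exposed after a reaction. The protocol itself notes that the drug has not been used in ME/CFS before and that experience outside malignant disease is limited.

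The second issue concerns the data. The primary outcome is safety and tolerability measured by treatment-emergent adverse events. Grade 1 events are left out of the reported set, so the line between grades 1 and 2 decides what is counted. Appendix 1 gives two ways of drawing that line. One of them refers to normal daily activity without saying whose normal, in patients who are mainly housebound or bedridden.

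**Working it through.** The main check is a comparison of text. There is no planned figure to reproduce.

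**Step 1. Do the body and the appendix share a vocabulary?** Yes. The Adverse events section pairs grade 2 with moderate, as Appendix 1 does. It is therefore reasonable to read severe in the stopping rule with its Appendix 1 meaning, grade 3. The rule is worded the same in two sections, so this is not a single misprint.

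**Step 2. What does each reading require?** The bracket can qualify both reactions or only the nearer one, and either the word or the number can be taken as decisive.

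| Reading | Grade 3 allergic reaction | Grade 3 injection-related reaction | Grade 4, either type |
|---|---|---|---|
| Number governs both | investigator's judgement | investigator's judgement | mandatory stop |
| Number governs injection-related only; allergic takes the Appendix 1 meaning of severe | mandatory stop | investigator's judgement | mandatory stop |
| Word governs both | mandatory stop | mandatory stop | mandatory stop |

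The readings agree at grade 4 and diverge only at grade 3.

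**Step 3. How often could it matter?** If all four added patients go on to maintenance, the plan allows 10 × 4 + 4 × 3 = 52 injections. Of these, 6 × 3 + 4 × 6 = 42 would be followed by another injection, so a reaction to them could affect re-dosing. The IRR section gives a 9% rate after the first injection in myeloma, usually grade 1 to 2, and expects a lower rate here. Taking 9% as the upper figure, 10 × 0.09 = 0.9 first-injection reactions of any grade would be expected. The documents give no grade 3 rate and no rate for later injections, so an expected number of grade 3 reactions cannot be calculated. For the first injection it lies below 0.9.

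**Step 4. Are the two grading instructions ranked?** Appendix 1 states both as operative and does not say which prevails if they disagree. Elsewhere the protocol names only CTCAE version 5.0: in the schedule footnotes and under Evaluations, Adverse events, and Documenting assessment and reporting of adverse events. Assessment during follow-up also has investigators assign CTCAE grades. The generic list appears once.

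**Step 5. Does the choice affect reported data?** Yes, at the boundary of grades 1 and 2. Data registration and management enters events of CTCAE grade 2 or higher. The Adverse events section reports from grade 2 upwards, and Documenting assessment and reporting of adverse events exempts grade 1. A grade above 1 is also part of the trigger for a clinic visit instead of a telephone call.

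**The case against.** The strongest reply is that the rule works in one direction only: it requires stopping at its trigger and nowhere instructs anyone to continue. A reader might infer that the protocol orders further dosing after a grade 3 reaction. The documents do not support that. The investigator may withdraw a participant at any time for safety, and adverse events and fitness for treatment are assessed before injections. The bracketed grade can also fairly be read as making a loose adjective precise. This limits the consequence to whether stopping at grade 3 is mandatory or discretionary, but it leaves that question open. A permission to withdraw is not the same as a duty to stop.

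A reader might also infer that the activity-based grades are at their ceiling because enrolled patients already meet the grade 3 description. That does not follow. Grades apply to events that are new or have worsened from baseline, not to standing disability, and unchanged pre-existing conditions are recorded separately. Patients are mainly, not wholly, housebound or bedridden; very severe disease is excluded; and grade 4 is described by threat to life. What remains is narrower. Those provisions decide whether something is an adverse event, not how a new event is graded in someone whose daily activity is already restricted.

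Finally, a reader might conclude that the primary safety table could not be interpreted. The primary outcome is not defined by grade. Each recorded event is described by duration, severity, suspected relationship and action taken, all serious events are reported whatever their cause, and with 10 patients events can be read one by one.

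**Conclusion.** The mismatch stands and should be corrected: the word and the number in the mandatory stopping rule disagree under the protocol's own definitions, in both places where the rule appears. The uncertainty is confined to grade 3 reactions and to whether the bracket covers allergic reactions. Such reactions are probably rare in this trial, but the rule exists for that situation and is cheap to correct.

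The conclusion assumes that the body of the protocol uses the grade labels of Appendix 1, which the reporting threshold supports. It takes no position on which grade should end treatment.

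The two unranked grading instructions are a secondary defect. They leave the grade 1/2 boundary, and so the set of reported events, less firmly defined than it should be. The documents do not show how many events would be graded differently.

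**What to change.** Reconcile the rule under Daratumumab dosing, injection, and injection-related reactions (IRR) and under Discontinuation of study intervention with the grade definitions in Appendix 1. Word and grade number should agree and should be stated separately for allergic and for injection-related reactions. The clinical team decides which grade governs.

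In Appendix 1, state that CTCAE version 5.0 sets the grade, and remove the generic list or mark it as subordinate. Where a criterion depends on activity, say that the investigator judges it against the patient's state before treatment. It should not be scored from the self-reported function level: that is a secondary efficacy outcome in an unblinded study, and using it would tie safety grading to efficacy reporting.

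The cost is a sentence in each of two body sections and a short edit to one appendix list, plus a one-time check of adverse events already graded to see whether any grade changes.

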#### Daratumumab dosing and administration

The anti-CD38 antibody daratumumab has not been tested previously in ME/CFS patients.

During recent years, small phase II studies have been published evaluating daratumumab in several autoimmune diseases, among them patients refractory to treatment including rituximab, cyclophosphamide and other immunomodulatory drugs.

In autoimmune hemolytic anemia (44), anti-phospholipid syndrome (45), treatment-refractory autoimmune cytopenias, cold agglutinin disease and other autoimmune diseases (ITP, systemic lupus, anti-CASPR2 encephalitis, rheumatoid arthritis), daratumumab has shown high efficacy in case series (46). In systemic lupus erythematosus, daratumumab was effective and clinical responses sustained by anti-BAFF (belimumab) maintenance treatment (47).

The use of daratumumab in ME/CFS is based on the pathomechanistic model suggesting that ME/CFS is a variant of an autoimmune disease with a role for autoantibodies, produced by long-lived plasma cells.

It is presently unknown what would be the optimal administration and dosing schedule in ME/CFS. Subcutaneous daratumumab 1800 mg is in multiple myeloma equivalent to intravenous daratumumab 16 mg/kg. Subcutaneous daratumumab in monotherapy has a half-life of 20.4 days.

We have based the suggested dosing schedule on the experiences from the above-mentioned studies in established autoimmune diseases. In these small case series of patients with warm-type autoimmune hemolytic anemia (wAIHA), the daratumumab administrations span from one, two, four, six and more than ten administrations, summarized in (46).

In one study of four patients with autoimmune hemolytic anemia (44), patients received repeated daratumumab infusions up to a maximum of six doses, including one patient who stopped treatment after three administrations due to a very good response, with lasting responses to end of follow-up after one year in two patients, and with no major side effects.

In other autoimmune diseases, pilot case reports have used four doses (immune-mediated thrombocytopenia after allogeneic stem cell transplantation; anti-phospholipid syndrome), four daratumumab doses (systemic lupus erythematosus) followed by anti-BAFF antibody belimumab maintenance, 10 administrations (anti-NMDA encephalitis) and 13 administrations (anti-CASPR2 encephalitis), summarized in (46).

Memory B-cells do not express significant amounts of CD38, and re-emergence of antibodies over time would be expected. According to our pathomechanistic hypothesis (13), with autoantibodies emerging after infection which persist and target blood vessel flow regulation, we believe that the ME/CFS disease is a reversible disease. We acknowledge that patients may also experience spontaneous remissions. We do not know if and when the putative autoantibodies will reappear after daratumumab intervention, but it is conceivable that a “resetting” of the plasma cell compartment could induce a sustained remission in some patients.

In this pilot study, we have in the original protocol not included any maintenance treatment to prolong possible clinical responses. We anticipate that four administrations of standard daratumumab dosing in each injection will be sufficient to assess feasibility and toxicity, and also to give indications for possible clinical benefit.

Based on observations of patients in the pilot study until March 2023, according to a second amendment, four additional patients will be included in the pilot study. For these four new patients, if clinically assessed improvement of ME/CFS symptoms at week 24, these will receive three additional daratumumab injections 8 weeks apart, i.e. at weeks 26, 34 and 42, and with prolonged follow-up until week 72.

A possible future larger study could verify or refute such efficacy, and if we observe clinical responses with limited duration after daratumumab, possible options include a prolonged daratumumab induction treatment or inclusion of a maintenance phase using e.g. B-cell depletion with rituximab, or anti-BAFF antibody treatment with belimumab.

### Drug handling

The pilot study is an open-label phase II study with no blinding or placebo group. Daratumumab will be available from the hospital pharmacy. Records of prescription and administration of daratumumab will be maintained through the medication management software Cytodose, as per standard department procedures.

Daratumumab must not be utilized after the expiry date printed on the label. Daratumumab must be protected from light and must not be frozen. When taken from storage at 2-8°C, the syringe will be used within 2 hours, and the vial must not be put back in the refrigerator. The product does not contain preservatives, therefore, any unused portion remaining in the vial must be discarded.

### Discontinuation of study intervention and participant discontinuation/withdrawal

#### Study termination

If any new information affecting the risk-benefit assessment should emerge, and upon the request of investigators or the Safety Board, sponsor will suspend the study pending a new risk-benefit assessment. If the new information indicates that the patient risks would outweigh the benefits, the study will be terminated.

If the study is prematurely terminated or suspended, the sponsor shall promptly inform the investigators, the regulatory authorities and the participants.

#### Discontinuation of study intervention

In rare instances, it may be necessary for a participant to permanently discontinue study intervention. If study intervention is permanently discontinued, the participant should, if at all

possible, remain in the study to be evaluated for safety and efficacy as described under “Assessment during follow-up”.

A participant may be withdrawn at any time at the discretion of the investigator for safety reasons, if the investigator considers that further intervention may present a danger to the patient’s health. If a patient suffers a severe allergic reaction or injection-related reaction (grade 4), the patient will not receive further daratumumab intervention.

#### Participant discontinuation/withdrawal

A participant may withdraw from the study at any time at the participant’s own request for any reason (or without providing any reason).

If the participant withdraws consent for disclosure of future information, the sponsor may retain and continue to use any data collected before such a withdrawal of consent.

If a participant withdraws from the study, the participant may request destruction of any samples taken and not tested, and the investigator must document this in the site study records.

#### Assessment during follow-up

After inclusion, patients will complete the questionnaires (SF36, DSQ-SF, self-reported Function level) at 2-week intervals for the first 28 weeks, then at 4-week intervals for the remaining 24 weeks (until 52 weeks). For the additional four included patients (according to amendment 2), if clinically assessed improvement at week 24, there will receive additional three daratumumab injections as described, and with prolonged follow-up until week 72.

Steps per 24h, Resting heart rate, and Heart rate variability will be registered by mean (and SD) per 2-week intervals for the first 28 weeks, then at 4-weeks intervals for the remaining 24 weeks (or 44 weeks if given maintenance) of the study.

Patients will be assessed at the outpatient clinic, Dept. of Oncology, at 12 weeks (end of run-in period before start of daratumumab intervention) and at 20 weeks (after the fourth daratumumab injection), 32 weeks and at end-of-study at 52 weeks.

At these visits (12, 20, 32, and 52 weeks) a clinical assessment with laboratory test will be performed, in addition to collection of self-report questionnaires and blood samples for biobank.

Patients will also be assessed by clinical examination and laboratory tests before each daratumumab injection at 14, 16 and 18 weeks. An investigator or study nurse will contact the patient by telephone 2 days before daratumumab injections number 2, 3 and 4, and the physician will assess the patient upon arrival at the outpatient clinic for planned daratumumab injections 2, 3 and 4.

The study nurse will record any complaints or side effects from intervention, and the investigators will assess the CTCAE grading.

To make participation in the pilot study less demanding for patients, further monthly assessments at 24, 28, 36, 40 and 44 weeks can be performed by telephone provided that the

patients experience no significant side effects. However, if the patient experiences significant side effects – i.e. side effects of CTCAE grade > 1, which require clinical examination and/or extra laboratory work-up, these visits should also be performed in the outpatient clinic.

The patients should use effective contraception measures from 4 weeks before start of intervention and until 24 weeks after last intervention (i.e. week 44).

In the intervention period (weeks 12-18) and for the following 14 weeks (i.e. until week 32) female patients of child-bearing potential must use highly effective contraceptive measures, and in this time interval the patients must perform a monthly serum pregnancy test (weeks 12, 16 and 20). Thereafter, in the time interval 24-32 weeks, pregnancy tests can be taken according to clinical indication.

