## Schedule of activities – including maintenance treatment

*For patients with symptom improvement after initial 4 injections*

|                                             | 0              | 2 | 4 | 6 | 8 | 10 | 12             | 14             | 16             | 18             | 20               | 22 | 24             | 26               | 28             | 32 | 34               | 36             | 40             |
|---------------------------------------------|----------------|---|---|---|---|----|----------------|----------------|----------------|----------------|------------------|----|----------------|------------------|----------------|----|------------------|----------------|----------------|
| Full clinical assessment a       | X              |   |   |   |   |    | X              |                |                |                | X                |    |                |                  |                |    | X                |                |                |
| Telephone consultation                      |                |   |   |   |   |    |                | X b | X b | X b |                  |    | X c | X b   | X c |    |                  | X c | X c |
| Safety assessment d              |                |   |   |   |   |    |                | X              | X              | X              |                  |    |                | X                |                |    | X                |                |                |
| Registration of adverse events e |                |   |   |   |   |    | X              | X              | X              | X              | X                | X  | X              | X                | X              |    | X                | X              | X              |
| General laboratory tests                    | X f |   |   |   |   |    | X g | X g | X g | X g | X g   |    |                | X g,o |                |    | X g,o |                |                |
| Serology                                    | X f |   |   |   |   |    |                |                |                |                |                  |    |                |                  |                |    |                  |                |                |

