| DSQ-SF                                      |                  | X              | X              | X                | X  | X              | X  | X  | X              | X              | X              |
| Function level                              |                  | X              | X              | X                | X  | X              | X  | X  | X              | X              | X              |
| HADS                                        |                  |                |                | X                |    |                |    |    |                |                |                |
| Download of Fitbit data                     |                  | X              | X              | X                | X  | X              | X  | X  | X              |                |                |
| NIRS assessment n                |                  |                | X              |                  |    |                |    |    |                |                |                |

a Full clinical assessment by investigator incl. laboratory tests, AE assessment and laboratory tests

b Telephone consultation by study nurse or investigator 2 days prior to treatment. Assessment of AEs and fitness for treatment.

c Telephone consultation by study nurse or investigator, monthly after treatment. In the case of AEs of CTCAE grade >1 which require clinical examination and/or extra laboratory workup, visit will be performed in outpatient clinic and not by telephone.

d Assessment by study nurse or investigator on day of treatment, prior to injection. Assessment of AEs and fitness for treatment.

e Classified by CTCAE version 5.0

f See protocol: Laboratory tests at baseline

g Hb, TC, DC, TBC, CRP, Na, K, Ca, Mg, P, Glu, Creatinine, eGFR, ALAT, ALP, GT, bilirubin, albumin.

h Plasma samples for anti-daratumumab antibodies

i Serum immunoglobulins (IgG, IgA, IgM) and lymphocyte subtypes in peripheral blood (CD19, CD3, CD4, CD8, CD56/CD16, ratio CD8/CD4)

j IgG subclasses (IgG1, 2, 3 and 4) and vaccination status: titers of antibodies to tetanus, diphtheria, pertussis and Covid-19.

k 6 ml EDTA plasma, 6 ml EDTA blood, 3x10 ml serum, 2x9 ml Tempus blood RNA

l 6 ml EDTA plasma, 2x10 ml serum

m On clinical indication only

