### Evaluations

Evaluation of safety and toxicity at 2-week intervals, for 16 weeks after start of intervention (from week 12 to week 28), then at 4-week intervals for the remaining follow-up (from weeks 29 to 52). For patients with clinical improvement at week 24, who receive additional three daratumumab injections, the evaluation of safety and toxicity will be extended to week 72. This will include registration according to CTCAE ver. 5.0 of adverse events (AE), serious adverse events (SAE), and SUSAR (suspected unexpected serious adverse reactions).

**Questionnaires** at 2-week intervals during the 12-week run-in period, and during the first 16 weeks after start of intervention, then at 4-week intervals for the remaining follow-up period (to week 52 for patients without maintenance, and to week 72 for patients with three additional maintenance injections).

The questionnaires include:

The Short Form (36) Health Survey (SF36).

DePaul questionnaire Short Form (DSQ-SF).

Function level in percent, according to a form with examples.

In addition, patients will complete the Hospital Anxiety and Depression Scale (HADS) questionnaire at baseline, at 24 weeks, and at 52 weeks.

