**At 12, 20, 32 and 52 weeks:**

Laboratory tests: Hemoglobin, leucocytes with differential count, thrombocytes, CRP, Na, K, Ca, Mg, phosphate, glucose, creatinine, eGFR, ALAT, ALP, GT, bilirubin, albumin.

At these visits, blood samples for biobank will be collected.

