**In addition:**

At the **20-week visit**, plasma samples for determination of anti-daratumumab antibodies will be collected.

At the visits at **12, 16 and 20 weeks, and if given maintenance at weeks 26, 34 and 42:** s-HCG.

At the visits at **weeks 14, 16, 20, 32 and 52, and if given maintenance at weeks 26, 34 and 42:** serum immunoglobulins (IgG, IgA, IgM) and lymphocyte subtypes in peripheral blood (CD19, CD3, CD4, CD8, CD56/16, ratio CD8/CD4).

Also at the **52 week visit:** IgG subclasses (IgG1, 2, 3 and 4), and vaccination status with titers of antibodies to tetanus, diphtheria, pertussis and Covid-19.

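### Maintenance patients: the text keeps a week-32 clinic visit, the maintenance schedule moves it to week 34, and 6 weeks pass without scheduled staff contact or adverse-event registration

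*Protocol*

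**What the plan says.** **Text.** The Assessment during follow-up section puts clinic visits at weeks 12, 20, 32 and 52: "At these visits (12, 20, 32, and 52 weeks) a clinical assessment with laboratory test will be performed". The laboratory and biobank paragraph that follows is headed "At 12, 20, 32 and 52 weeks". Neither exempts patients on maintenance, although the same section does mention maintenance for the length of follow-up and the Fitbit intervals. The immunology list, under In addition, adds maintenance weeks to week 32 and does not replace it: "weeks 14, 16, 20, 32 and 52, and if given maintenance at weeks 26, 34 and 42". Between clinic visits, "further monthly assessments at 24, 28, 36, 40 and 44 weeks can be performed by telephone". Week 32 is absent from that list because it is a clinic visit there.

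The Evaluations section sets safety and toxicity evaluation every 2 weeks to week 28, "then at 4-week intervals for the remaining follow-up (from weeks 29 to 52"). Its next sentence deals with maintenance patients and changes only the end date, to week 72.

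**Maintenance schedule.** The table, captioned "For patients with symptom improvement after initial 4 injections", has the full clinical assessment, laboratory tests, immunology and biobank sample at week 34. At week 32 it has only the questionnaires (SF-36, DSQ-SF, function level) and the Fitbit download. The telephone, safety-assessment and adverse-event rows are blank at week 32. Footnote c describes the routine calls as "Telephone consultation by study nurse or investigator, monthly after treatment". Footnote b describes the pre-dose call as "Telephone consultation by study nurse or investigator 2 days prior to treatment"; it is marked at week 26 (injection 5) but not at week 34 (injection 6).

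**Biobank sections.** Both the sampling and the collection sections replace week 32 with weeks 34 and 42 when maintenance is given.

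**The concern.** The text and the maintenance schedule give different instructions for the same patients. For the biobank sample, the text also disagrees with itself. When the clinic visit moved to week 34 in the maintenance schedule, nothing took over the safety contact that week 32 had provided.

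The primary outcome is treatment-emergent adverse events. In this interval, which lies between injections 5 and 6, the patients given the most drug are asked about events less often than the Evaluations section states, and less often than patients without maintenance. This affects when staff ask, not which events count. What can suffer is recall, or prompt detection, of a transient event after injection 5.

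Staff could satisfy both versions, apart from the biobank draw, by seeing the patient at weeks 32 and 34. That would mean two trips within two weeks for someone mainly housebound or bedridden, in a protocol that uses telephone assessments to lighten participation.

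**Working it through.** The inputs are the two schedules of activities, read by column against their week headings, and the interval in the Evaluations section. Each interval is the later week minus the earlier one.

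**1. Schedule without maintenance.** Adverse-event registration from week 28: 28, 32, 36, 40, 44, 48, 52. Every interval is 4 weeks, which reproduces the interval in the Evaluations section.

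**2. Maintenance schedule.** Adverse-event registration from week 28: 28, 34, 36, 40, 42, 44, 48, 52. The intervals are 6, 2, 4, 2, 2, 4, 4, with a maximum of 6. Staff contacts are by telephone at 28, 36, 40, 44 and 48 and in clinic at 34, 42 and 52, so they fall on the same weeks. Of the 4-weekly points from 28 to 52, only week 32 is missing.

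**3. Position relative to dosing.** Injection 5 is at week 26. The next contacts come 28 − 26 = 2 weeks and 34 − 26 = 8 weeks later, the second being the day of injection 6. If a pre-dose call were made two days before week 34 although none is marked, the interval from week 28 would still be 6 × 7 − 2 = 40 days, against 28.

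**4. Week 32 for maintenance patients, text against table.**

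| Item | Text | Maintenance schedule |
|---|---|---|
| Clinical assessment | week 32 | week 34 |
| Laboratory tests | week 32 (and 34) | week 34 |
| Immunology | week 32 (and 34) | week 34 |
| Biobank | week 32 (follow-up section); week 34 (biobank sections) | week 34 |
| Safety evaluation | week 32, from the 4-week interval | none between 28 and 34 |

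With at most four maintenance patients, each row concerns at most four occasions.

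**5. What is not claimed.** After injection 5 the first laboratory set comes at 32 − 26 = 6 weeks by the text and 34 − 26 = 8 weeks by the table. After injection 6 it comes at 42 − 34 = 8 weeks under both, so an 8-week laboratory lag is not treated as a deficiency. The table's intervals after week 52 (52 to 60 and 60 to 72) are longer, but the Evaluations section states no interval for that period and they are not challenged.

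**6. With a contact and registration added at week 32.** The weeks become 28, 32, 34, 36, 40, 42, 44, 48, 52. The intervals are 4, 2, 2, 4, 2, 2, 4, 4, with a maximum of 4.

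**The case against.** The strongest reply is that this is leftover wording from an amendment. A dedicated maintenance schedule exists, the biobank sections agree with it, and staff using it have a clear instruction.

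Surveillance overall is also heavier on maintenance. After week 28 and up to week 52 there are 7 adverse-event registrations (34, 36, 40, 42, 44, 48, 52) against 6 without maintenance, and three full clinical assessments (34, 42, 52) against two (32, 52). The missing pre-dose call fits a pattern: calls are marked before injections that have no full assessment (weeks 14, 16, 18, 26) and not before those that have one (12, 34, 42). Dosing at week 34 is protected by the same-day assessment, and pre-dose bloods may be drawn locally up to a week earlier.

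Appendix 1 requires events to be reported from consent to end of study, patients have direct access to the study team, and grade 1 events are not reported at all.

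Most of this is correct and keeps the point small. It does not remove the conflict. The Evaluations section gives maintenance patients no longer interval before week 52, and the In addition list names weeks 32 and 34 together. Questionnaires, Fitbit data and a local blood draw are not adverse-event registration. A higher total count does not shorten this interval, and Appendix 1 ties active assessment of events to the evaluation time points. Rewording the Evaluations section to name week 34 would settle the contradiction but leave the 6-week gap.

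**Conclusion.** The point holds and is minor. For maintenance patients the text and the maintenance schedule disagree about week 32, and the schedule leaves 6 weeks (28 to 34) without scheduled staff contact or adverse-event registration where the protocol states 4. It is the only interval above 4 weeks between weeks 28 and 52. It concerns at most the four additional patients, and only those who go on to maintenance.

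This rests on two readings: that the 4-week interval applies to maintenance patients, since the sentence about them changes only the end date; and that contact means contact with staff, since questionnaires and the Fitbit download remain at week 32. No effect on which events are reportable is claimed. The exposure is limited to recall or late detection of a transient event of grade 2 or higher after injection 5.

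**What to change.** 1. In Assessment during follow-up, including the paragraph on weeks 12, 20, 32 and 52 and the In addition list, limit the week-32 visit, laboratory tests, immunology and biobank sample to patients without maintenance. Weeks 34 and 42 already appear for maintenance under the laboratory, immunology and biobank provisions and need no repeat.
2. In the maintenance schedule, mark a telephone consultation (footnote c) and adverse-event registration at week 32. That week already holds the questionnaires and Fitbit download and is one of the fixed analysis time points in Endpoints and statistical analyses.

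The cost is wording in three places, two marks in one table, and one call per maintenance patient: 1 × 4 = at most 4 calls in the study. No visit or blood sample is added, and a possible duplicate trip two weeks before the week-34 injection is removed.
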